### Intervention

Two intervention strategies to increase retention in care (primary outcome), as well as linkage to care, ART adherence, and prevention behaviors (secondary outcomes) will be compared to local standard of care (SOC). The two intervention strategies that participants will receive for the duration of 1 year are as follows: 1) an automated SMS and 2) a peer-navigator (PN) model that also includes some automated SMS.

The first strategy includes three types of messages to be sent to participants that will be delivered automatically from a central system based on their gender and clinical/ART status recorded on registration and enrollment forms and updated through clinical record extraction (Fig. 2). These three message types include the following:Behavioral Messages: These messages are sent on a biweekly (every other week) basis, for a total of 26 messages during the 1-year study period. Behavioral messages are designed to address four themes: HIV prevention (some of these messages are gender-specific); engagement in care; medication adherence (for those on ART) or awareness (for those not yet eligible for treatment); and healthy living, which includes messaging concerning alcohol/drug use, social support and safe disclosure, and health/nutrition.Care Reminder Messages: Participants are sent a message 3 days before any scheduled clinic visits, whether for ART refills, CD4+ or HIV viral load testing, or other routine care. Participants also receive a reminder message if they have missed a clinic visit by over 2 weeks, in line with South African guidelines [13]. Patients receive up to 6 messages (bi-weekly) following a missed appointment to encourage them to return to the clinic. Additionally, when a client has failed to present for a visit for 3 months, the study staff will alert the clinic that a client has been lost to follow-up.Two-way Messages: These are automated biweekly “check-in” messages that are sent from a central system; they also record participant responses and send a system alert to the team if a follow-up call to the participant is needed. Two-way messaging serves to maintain contact with the participant, provides a means of retention in the study and in care, and also is a probe to ensure that the participant is not defaulting on care and treatment or experiencing any difficulties that need to be addressed. The participant receives a request to “reply 1 if you’re good or 2 if you have a problem and need to talk.” If the participant responds “2,” project staff will receive an alert to call the client within the first business day after receiving the notification. If the participant does not respond to the check-in message within 24 hours, the participant receives the message a second time. If the participant has not replied to either message after 48 hours, the study staff will receive an alert to call the client. When staff call for either a “2” response or a non-response, they follow a protocol for referrals and are trained not to offer advice and counseling. Responding to two-way messages is free of cost for participants.

**Fig. 2 Fig2:**
[figure not shown]
Map of the principal data collection and intervention activities across three study arms. Abbreviations used in the figure: ART = Antiretroviral Therapy; SMS = Short Message Service (i.e., Text Message)

The automated messaging system provides scheduled delivery of messages via the CommConnect online platform, part of the CommCare system developed by Dimagi, Inc. The particular behavioral messages that a participant receives are determined by gender and ART status, as captured by study staff during enrollment. The ART status classification is also linked to ongoing clinic record extraction, so that if the ART status changes, so does the message tree. Reminder messages are triggered by a “date of next appointment” field, which is updated during weekly chart extraction by study staff. If chart extraction indicates that a participant has missed a visit by over 2 weeks, a reminder is also sent. The CommConnect system sends and receives messages free of cost to participants. Even so, the study provides each participant with 50 to 60 Rand of airtime on the participant’s cell phone carrier of choice at enrollment and again at the 6-month follow-up visit to ensure that participants are comfortable using their phones for responding to study check-in messages.

The second intervention strategy is predicated on relationship building and support with fellow patients. Specifically, the strategy makes use of peer navigators, who work with participants to assess their barriers to retention in HIV care, ART adherence, and prevention of further HIV transmission, and then aids participants in developing plans and strategies for overcoming these barriers. To be eligible to serve as a peer navigator, a person must be HIV-positive, receiving care at a government-run primary healthcare facility, and have demonstrated commitment to adhering to medications and clinical monitoring. Each navigator will assist approximately 10 participants (no more than 12) during the study. Following an initial visit, navigators aim to have at least one in-person meeting and one check-in by SMS or phone with each participant each month (that is, a minimum of two contacts per month for 12 months). This standardized contact schedule is intended to serve as a minimum threshold. A navigator’s work with a participant will often involve additional contacts in the course of a month, such as offering to accompany a participant to their appointments (with participant consent), assisting a participant with disclosure of his or her HIV status to a family member or friend, or conducting additional meetings by phone or in-person to discuss emerging challenges and strategize solutions.

Participants in the peer navigator condition will also receive biweekly behavioral messages and appointment reminders, which will be sent via the CommConnect system according to the same schedule as used in the SMS-only strategy. Following the pilot of these strategies in four clinics, the study team resolved to include automated reminders and behavioral messages instead of personalized reminders and behavioral messages sent by the navigators to clients in the peer navigation arm. This decision ensures better consistency of messaging because navigators in the pilot phase struggled to personalize the sequencing of the various behavioral messages while still adhering to standardized scripts for each message. Additionally, investigators felt that automating the messages for clients in the PN arm would facilitate exploration of incremental effectiveness of the two study interventions, with one (PN) building on the other (SMS).

Peer navigators will meet weekly with their direct supervisors and biweekly with the larger study team to discuss challenges being observed among participants, and to develop potential approaches to overcome the observed challenges. In addition, the supervisory team meets weekly with study investigators to identify emerging complex challenges with particular participants or navigators, and to strategize solutions. Navigators also have access to a “clinic liaison” at each clinic site. This individual, usually one of the nurse providers, serves as a primary point of contact between the study team and clinic staff at a site. Navigators can refer their participants to the clinic liaison when, for example, they feel that a participant has a problem that requires medical attention or a referral for other medical or social services.

### Data collection procedures

Regardless of the intervention assignment, all participants, including those receiving services in the SOC clinics, are asked to complete a baseline survey assessment and provide contact information on the day that enrollment occurs. Participants will be reassessed via surveys during the 6-month and 12-month follow-ups. Both baseline and follow-up assessments will capture information about (1) access to clinics and HIV care services received in the 6 months preceding each assessment, (2) self-reported assessments of ART adherence (for participants on ART), and (3) self-reported HIV risk behaviors and risk reduction practices (condom use or partner reduction). The follow-up surveys also capture (4) self-reported receipt of the intervention components (for participants in the intervention arms) and (5) self-reported satisfaction with SMS and peer navigator services. We will also capture data related to demographics, disclosure, anticipated stigma [39], alcohol use (AUDIT-C) [40, 41], and mental health (CESD-10) [41, 42].

Data regarding clinical visits and care received will be extracted from clinical files. Record extraction will occur weekly for participants on ART, and every 2 weeks for those not on ART, who are seen less frequently than the ART patients. Study staff will capture details regarding any visit that occurred since the last extraction, including the visit date, HIV-related services received (for example, medications), and any related CD4+ or HIV viral load test results. All data collection forms and procedures have been reviewed and approved by the Committee for Human Research at the University of California, San Francisco (UCSF), the Human Subjects Division at University of Washington, and the Human Sciences Research Council (HSRC) Research Ethics Committee in South Africa. The Policy, Planning, Research, Monitoring and Evaluation Committee for the North West Provincial Department of Health also reviewed and approved the protocol.

We will also conduct microcosting of the resources needed to carry out the activities in all arms of the intervention. Costing will include the following: 1) personnel (including fringe benefits), 2) recurring supplies and services, 3) capital and equipment (for example, furniture and computers), and 4) facility space. Intervention costs will be assessed using a uniform cost data-collection protocol to quantify resources used and associated costs in each of the study arms. Data will be obtained through administrative record reviews and administrative and program staff interviews, supplemented by a staff time study in order to distinguish pre-implementation and implementation activities. Pre-implementation includes hiring, procurement, intervention development/modification and training. Implementation includes recruitment, intervention activities and supervision. Nonresearch program management costs will be allocated based on the period in which they occurred (pre-implementation versus implementation).

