### Measures

Primary and secondary exposure and outcome measures are included in Table 1. Primary exposure for the intent-to-treat analysis is classified as the clinic randomization arm: SMS intervention, PN intervention, and SOC. The primary study outcome is retention in care, which is defined for patients on ART as the proportion of patients who have initiated ART who remain on treatment at 6 and 12 months and for patients who are not yet eligible as the proportion of patients who undergo a repeat CD4 test at 6 months and 12 months after the initial CD4. The secondary outcome of linkage to care is defined as a patient undergoing CD4 staging or being assessed for ART eligibility within 3 months of a positive diagnosis. We will also monitor whether the participants are linked to ART – that is, whether eligible participants receive ART within 3 months of CD4 staging. The secondary outcome of adherence is being assessed in three ways: as a report of taking 90 % of the prescribed medication, as no report or clinical record indicating gaps in treatment of 4 or more days, and collection of the proportion of days covered by medication dispensed. Finally, prevention behavior is defined as the number of unprotected sex acts by HIV partner status. All outcomes will be measured using both clinical record extraction and self-report; these two means of data collection will be compared for accuracy (using clinical record extraction as the gold standard).

**Table 1 Tab1:** Measures, data sources, and data collection schedules for protocol exposures and outcomes

Domain	Instrument/measure	Data source	Data collection schedule
PRIMARY EXPOSURE			
Clinic randomization assignment	Clinic where participant receives care	Intake form	Baseline
SECONDARY EXPOSURE			
Intervention Dosage	Minutes of intervention received	PN participant contact forms and CommConnect system records	Ongoing capture
PRIMARY OUTCOMES			
Retention in HIV care	Patients on or initiating ART who remain on treatment 6 and 12 months later (with documented receipt of treatment)	Intake and Record extraction	Weekly (ART)
		Survey data (self-report)	0, 6, and 12 months
	Patients not ART eligible who have a repeat CD4 test at 6 months and 12 months after initial CD4	Intake and Record extraction	Bi-weekly (pre-ART)
		Survey data (self-report)	0, 6, and 12 months
SECONDARY OUTCOMES			

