Linkage to HIV care	CD4 drawn and results available at clinic within 3 months of testing HIV positive	Intake and Record extraction	Weekly (ART) bi-weekly (pre-ART)
	CD4 result received within 3 months of testing HIV positive	Survey data (self-report)	0 and 6 months
	Patients eligible for ART who initiate treatment within 3 months of CD4 staging	Intake and Record extraction	Weekly (ART)
		Survey data (self-report)	0, 6, and 12 months
Adherence to ART	Proportion taking 90 % and 100 % of pills in the past 30 days	Survey data (self-report)	0, 6, and 12 months
	Breaks in treatment during the previous six months (at least 4 days in a row)	Intake and Record extraction	Weekly (ART)
		Survey data (self-report)	0, 6, and 12 months
	Proportion of days covered (# of dispensed days of medication/# of days between refills)	Intake and Record extraction	Weekly (ART)
Prevention (transmission risk)	Number of unprotected sex acts by partner HIV status	Survey data (self-report)	0, 6, and 12 months

Because the volume and intensity of the intervention might vary, particularly in the PN arm, we will also capture intervention exposure or dosage as a secondary exposure measure. Dose (minutes) of intervention received will be used for per protocol analyses. In the PN arm, this will include recording client data on frequency and duration of in-person meetings and phone communications with the navigator. Delivery and response to SMS messages for both intervention arms will be recorded with a standard duration of exposure (for example, 30 seconds) for each message, including two-way messaging. Any phone or in-person follow-up to SMS messages will be recorded separately. Secondary outcomes include linkage to HIV care, adherence to medications, and transmission risk behavior, as described in Table 1.

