### Analysis

Our preliminary analysis will include presentation of participant demographic characteristics, service usage, acceptability of intervention approaches and self-reported sexual behavior within each of the three study arms using descriptive statistics (one-way and cross-tabular frequency tables and, for continuous variables, measures of central tendency). Measures of variability will account for repeated measures (multiple patients) and consequent correlation of variables (clustering) within each health facility. We will employ multiple imputation (MI) using chained equations to account for missing data. This procedure assumes that incomplete data arise from a missing-at-random (MAR) process, under which missingness is random conditional on observed covariables and observed outcomes rather than a missing-completely-at-random (MCAR) mechanism [43], thus making fewer assumptions about the nature of the missing data. We will conduct sensitivity analysis using weighted MI to evaluate the robustness of the MAR assumption [44].

Our primary analyses will employ an intention-to-treat (ITT) approach. We will employ logistic generalized estimating equations (GEE) to compare patient retention between intervention arms. We will also evaluate secondary outcomes (linkage, adherence and prevention behaviors) using an ITT analysis, as described above. We will employ GEE rather than mixed effects models as this approach allows us to estimate the effect of the intervention at the level of the population, rather than at the level of the individual. As our interventions will be implemented at the level of the health system, it is important to estimate the effect of the intervention at the level it is implemented [45]. Further, previous research has suggested that adjustment for confounding can improve the efficiency of estimates in the context of randomized trials [46]. We will thus conduct sensitivity analyses employing causal inference methods to account for any imbalance in distribution of site- and individual-level co-variables across study clinics. We will employ targeted maximum likelihood estimation [47], which allows estimation of both site- and individual-level co-variables, to minimize bias and improve efficiency of estimates of effect in the context of small sample sizes [48].

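### Self-reported pill-taking appears to be asked only of participants on ART at each survey, so the comparison called ITT is made in a group selected by the primary outcome

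*Protocol article*

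**What the plan says.** Data collection procedures: the baseline and follow-up surveys capture "self-reported assessments of ART adherence (for participants on ART", the bracket closing there. The next paragraph separates weekly record extraction for those on ART from two-weekly extraction for those not on ART.

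Measures and Table 1 give three adherence measures:

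- "Proportion taking 90 % and 100 % of pills in the past 30 days", with the survey at 0, 6 and 12 months as its only listed source.
- Treatment breaks: "Breaks in treatment during the previous six months (at least 4 days in a row", from both record extraction and survey. The text of Measures words this as "as no report or clinical record indicating gaps in treatment of 4 or more days".
- Days covered by dispensed medication, from records only.

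For ART patients the primary outcome is the "proportion of patients who have initiated ART who remain on treatment at 6 and 12 months".

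Analysis: "We will also evaluate secondary outcomes (linkage, adherence and prevention behaviors) using an ITT analysis, as described above". On incomplete data: "We will employ multiple imputation (MI) using chained equations to account for missing data", under a missing-at-random assumption. The article gives no adherence denominator and no value for a participant who has stopped ART.

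**The concern.** A participant who stopped ART more than 30 days before the survey took none of the pills in the 30-day window. That person is a clear failure on the 90 % and 100 % criteria, but contributes no value if the item is asked only of people currently on ART. Who contributes is then decided by whether the participant stayed on treatment, which is what the interventions are meant to change and what the primary outcome measures.

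An arm that holds on to more patients with difficulties brings them into its adherence denominator. In the comparison arm the same kind of patient has left it. The two groups are no longer those formed by randomisation, so the ITT label does not fit. A successful retention intervention could be reported as having no effect on adherence, or a harmful one.

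**Working it through.** **1. Which reading of the collection rule?** The bracket could mean currently on ART or ever started. The paragraph that follows it contrasts participants on ART with those not on ART as a current status. The Intervention section also treats ART status as something that changes and is updated from the records. Current status at the survey is the natural reading, though the words are not written.

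**2. Can another source fill the value?** Table 1 lists only the survey for the 90 %/100 % measure, so the listed sources do not supply it for someone not asked. Imputation under missing at random would draw on people still on ART, although a documented stopper is already known to fall below both thresholds.

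**3. Size.** The article states no adherence figure, so there is nothing to reproduce. Let r0 and r1 be the proportions of ART starters still on ART (SOC, intervention), a the adherence of those who would stay in either arm, and b the adherence of the extra patients kept on ART only by the intervention. Assume first that a is the same in both arms.

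- Among those on ART: SOC = a; intervention = [r0·a + (r1 − r0)·b] / r1; difference = (r1 − r0)(b − a) / r1.
- Among all starters, with stoppers as non-adherent: SOC = r0·a; intervention = r0·a + (r1 − r0)·b; difference = (r1 − r0)·b.

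All four quantities are assumptions. The 50 % and the 20 to 23 points are borrowed from Sample size estimation, where they refer to retention in care and not to persistence on ART.

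| r0 v r1 | a, b | On ART (SOC v intervention) | All starters (SOC v intervention) |
|---|---|---|---|
| 50 % v 70 % | 85 %, 60 % | 42.5/50 = 85.0 % v (42.5 + 12)/70 = 77.9 %: −7.1 | 42.5 % v 54.5 %: +12.0 |
| 80 % v 90 % | 85 %, 60 % | 68/80 = 85.0 % v (68 + 6)/90 = 82.2 %: −2.8 | 68 % v 74 %: +6.0 |
| 50 % v 73 % | 90 %, 30 % | 90.0 % v (45 + 6.9)/73 = 71.1 %: −18.9 | 45.0 % v 51.9 %: +6.9 |
| 50 % v 70 % | 80 %, 80 % | 80.0 % v 80.0 %: 0.0 | 40 % v 56 %: +16.0 |

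Over a = 80 to 90 %, b = 30 to 80 % and 50 % v 70 to 73 % on ART, the on-ART difference runs from −18.9 to 0.0 points and the all-starters difference from +6.0 to +18.4.

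**4. When does the sign not change?** If the intervention also raises adherence to x in those who would have stayed anyway, the on-ART comparison favours it once:

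- at 50 % v 70 %: (50x + 12)/70 > 0.85, so x > 47.5/50 = 95 %;
- at 80 % v 90 %: (80x + 6)/90 > 0.85, so x > 70.5/80 = 88.1 %.

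The downward pull from the extra patients remains in both cases, but the sign does not have to flip.

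**The case against.** **The wording.** Measures uses patients on ART loosely for those who have initiated it, and the bracket may only be there to exempt participants not yet eligible. If it means ever started, stoppers are asked and most of the problem disappears. This is possible, and it is why the point rests on the natural reading. The wording would still need fixing. A later analysis plan could add a scoring rule, but it could not recover survey items that were never asked.

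**The break measure.** A reader might infer from the definition by absence of a report that someone who stops attending is scored as gap-free. The documents do not support this. Breaks are also taken from weekly record extraction, Measures makes the records the gold standard, and missed visits are tracked. No passage scores silence as adherence. This measure is affected less, through the loss of its self-report part.

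**The size.** A reader might take the planned 50 % as the share of SOC starters still on ART, or conclude that the sign always reverses. Neither holds. The 50 % is retention in care for all SOC participants, and the article gives no figure for ART persistence. Reversal depends on the assumed rates and on no sufficiently large effect in the always-retained. Both interventions address adherence directly, so such an effect is plausible.

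**The remedy.** Adherence among treated patients is a legitimate question, and counting stoppers as failures makes the measure partly repeat retention. The article also expects about 20 % to discontinue, mostly through migration. Scoring every absence of dispensing as a gap would misclassify people who continue ART elsewhere. Both objections stand and limit the fix below.

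**Conclusion.** The point holds for one secondary measure. On the natural reading of Data collection procedures, the self-reported 90 %/100 % pill measure is compared among people selected by the primary outcome while being labelled ITT. If the extra patients kept on ART adhere less well than those who would have stayed anyway, the comparison is biased against the better-retaining arm. If they adhere equally well, there is no downward bias, but the gain from keeping them on ART does not show.

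In the illustrations with 85 % and 60 % adherence, the on-ART contrast is about 3 to 7 points against the intervention, while the all-starters contrast is 6 to 12 points in its favour. These sizes rest on assumed adherence and persistence, on equal adherence of the always-retained across arms, and on everyone who would stay on ART under SOC also staying under the intervention. The primary retention comparison and the sample size are not touched.

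**What to change.** - **Collection:** ask the pill-taking and break items of every participant who has ever started ART, whatever their status at the survey.
- **ITT comparison:** use all known ART starters as the denominator. Score those who report, or whose records show, that they stopped ART as not meeting the 90 % and 100 % criteria and as having a break.
- **Unknown status:** treat participants known to have moved or transferred, or whose status is unknown, as missing, with the planned imputation and a sensitivity analysis. Do not count missing dispensing automatically as a gap.
- **On-ART version:** keep it, labelled as descriptive and conditional on still being on ART.

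The cost is one change to the survey skip pattern and a scoring rule, using record extraction that is already done. Recruitment began in October 2014, so some 6-month surveys may already be complete. For these, stopping can be taken only from the records. Headline adherence will be lower and will overlap in part with retention. The starters denominator is itself set after randomisation, so the change removes most of the selection but not all of it. It also does not reach people who miss the survey.
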